#### External support and practice implementation tracking

It is important for this evaluation to track characteristics of the interventions delivered to practices, including the type and intensity of external support interventions received, along with changes that practices implement to increase ABCS delivery. The ESCALATES team will work with Cooperatives to establish methods (e.g., practice facilitator contact logs, collaborative (onsite) or webinar attendance records) to track the type, frequency, duration and mode of external support provided to practices and their engagement with it. Data collection related to external support will continue throughout each Cooperative’s active intervention period, which will vary by Cooperative. The ESCALATES team will also work with Cooperatives to develop mutually agreeable methods to track and share the change strategies practices implement to improve ABCS (e.g., registries, standing orders) and the extent to which these changes are implemented within these practices.

#### Practice site visits

The ESCALATES team will also conduct practice site visits. We will purposively select a sample of 40–60 practices using both qualitative and quantitative data to do so. The ESCALATES team will develop a matrix that ranks practices by ABCS outcomes at baseline (from high to low), and will also include percent change in ABCS over study period, Cooperative, ownership, and characteristics relevant to the region within the Cooperative (e.g., rural, underserved) where relevant. The ESCALATES team will use this matrix of quantitative information along with qualitative implementation data to select a maximum variation sample of high and low performing practices, approximately six–eight per Cooperative. We will conduct preliminary analyses based on the first two–three visits and use this information to revise sample selection criteria as needed. This iterative process of selecting practices, collecting data, and using this information to refine sampling decisions will continue until variations in outcomes are adequately explained as indicated by theme saturation.

The ESCALATES team will work with Cooperative teams to invite practices to participate. Practices will receive a monetary fee for their time and participation. A multi-person team will spend 1–2 days in a practice intensively observing how ABCS care is delivered and conduct interviews (scheduled to minimize disruption) with practice members to understand their experiences with external support and their efforts to implement interventions aimed at increasing delivery of ABCS. Interviews will also identify practice, organization and contextual factors influencing implementation. Interviews guides and observation templates will be refined and tailored to each practice and to each member based on information from online diaries, Cooperatives, member role, and site visit preparation calls with practice members.

#### Patient pathways

At each site visit, study staff will conduct five–ten patient pathways [50]. Patient pathways are designed to observe patients’ exposures to and experiences with how the practice has implemented changes. Front desk staff will alert a field researcher when a patient meeting sampling criteria checks-in. The field researcher will ask the doctor and patient for permission to observe the visit. If both agree, the field researcher will follow the patient through the visit (e.g., intake, visit with clinician, check-out), being unobtrusive and making brief notes to be written up later as fieldnotes.

### Analytic strategy

This study aims to answer the following research questions:

*Cross-sectional research questions (baseline):*
What are the rates of meeting ABCS performance goals/targets among a large sample (>1500) of small- and medium-size primary care practices?What are the practice, organizational and contextual factors associated with varying degrees of meeting ABCS performance goals/targets at baseline (prior to implementing any intervention)?

*Longitudinal Research Questions:*
What are the types of intervention strategies (e.g. receiving different external support) implemented by Cooperatives, and how do they develop infrastructure for delivering these strategies to practices?Across practices, what are the effects of intervention strategies on change in practice processes and ABCS performance measures and practice capacity (e.g., CPCQ, adaptive reserve) over time, and how do these intervention strategies interact with practice, organization, and contextual factors to explain the observed change?Across practices, why are some intervention strategies more effective than others?What are the explanations for variation in outcomes across Cooperatives on ABCS and practice capacity outcomes (e.g., how do high and low performing practices differ, and how do intervention strategies and intensity, practice and organization characteristics contribute to these differences)?

Below, we describe the analytic strategy we will use to answer study research questions:

### Cross-sectional research questions (baseline)

At baseline (pre-intervention), the ESCALATES team will determine the overall rates of meeting ABCS performance targets across Cooperatives. These data will provide nationally representative estimates of ABCS delivery rates among small- to medium-size primary care practices, identify the current status of ABCS target attainment, and determine how much room for improvement is available over the study period.

The ESCALATES team will then evaluate the practice, organizational and contextual factors associated with ABCS performance prior to implementing an intervention. Initial analyses will be descriptive, using data visualization methods. The principal outcome of interest is the proportion of eligible patients meeting ABCS performance goals for each practice (i.e., continuous values from 0 to 1). We will perform univariable and multivariable beta regressions with variable dispersion [51]. Beta regression models are common in analysis of rates and proportions. We will use survey measures informed by the CFIR and PCM to construct independent variable selection models that help to identify relevant variables among many potential candidates to achieve better interpretability and uncover previously unknown relationships in the data. Variable selection for the proposed beta regression model will be performed using a regularization technique [52] similar to the adaptive LASSO (regression analysis). The ESCALATES team will select the final model based on the Bayesian information criterion (BIC) by choosing the tuning parameter with the lowest BIC value because regularization-type methods with a BIC-type tuning parameter selector, under certain criteria, have been shown to do consistent variable selection [53].

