## Background

The Agency for Healthcare Research and Quality (AHRQ) launched the EvidenceNOW Initiative in 2015 to promote delivery of evidence-based cardiovascular disease (CVD) preventive care in smaller primary care practices with limited resources and experience with quality improvement (QI), and to expand the nation’s capacity to rapidly translate evidence into practice. AHRQ funded seven regional Cooperatives spanning 12 states in the USA. Each Cooperative received a 3-year grant to create a health practice extension infrastructure to implement interventions aimed at decreasing cardiovascular risk for their patient populations within approximately 250 primary care practices, each with less than ten clinicians and with limited quality improvement capacity. Along with providing active external support, the Cooperatives will evaluate practice improvement efforts. In the call for proposals, AHRQ required use of measures that are common across the Cooperatives, including measures of CVD clinical quality and practice capacity outcomes. Cooperatives are required to share these data with a national evaluation team, which AHRQ funded separately.

This paper describes the study protocol for the EvidenceNOW national evaluation, called Evaluating System Change to Advance Learning and Take Evidence to Scale (ESCALATES) which aims to comprehensively evaluate the dissemination and implementation (D&I) approaches of the seven Cooperatives to generate overarching, cross-Cooperative findings. This work will inform future large-scale D&I efforts and expand the understanding of the characteristics of effective practice facilitation and regional extension services for practice improvement.

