### Study setting and population

EvidenceNOW Cooperatives will support practices in 12 US states and are each partnering with local collaborators (e.g., regional extension centers, quality improvement organizations) to engage smaller primary care practices in their regions. At the Cooperative level, the study sample includes the following regions: Midwest: Illinois, Indiana and Wisconsin (Principal Investigator (PI): [name]); New York City (PI: [name]); North Carolina (PI: [name]); Northwest: Washington, Oregon and Idaho (PI: [name]); Oklahoma (PI, [name]); Southwest: Colorado and New Mexico (PI: [name]); and Virginia (PI: [name]). The ESCALATES evaluation will include the approximately 1,500 primary care practices, their staff members, and patients across the Cooperatives.

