### Trial status

The ESCALATES team has engaged the seven Cooperatives in the data harmonizing process, conducted one site visit with each Cooperative, and are working to refine a common set of measures and procedures for data collection. Cooperatives’ recruitment of practices is in progress. The start of baseline data collection and implementation of interventions will vary by Cooperative with start dates scheduled between January 2016 and April 2016.

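### The baseline rates are called nationally representative, but the design describes practices recruited by seven regional Cooperatives and limited in QI capacity

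*Protocol article*

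**What the plan says.** The section Cross-sectional research questions (baseline) first describes the calculation: "the ESCALATES team will determine the overall rates of meeting ABCS performance targets across Cooperatives". It then states what the result will be: "These data will provide nationally representative estimates of ABCS delivery rates among small- to medium-size primary care practices". No qualifier is attached.

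Elsewhere the article describes where the practices come from:

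- **Regions (Background):** "AHRQ funded seven regional Cooperatives spanning 12 states in the USA". Study setting and population lists the seven regions. New York enters through New York City alone.
- **Type of practice (Background):** the practices to be supported are "each with less than ten clinicians and with limited quality improvement capacity".
- **Route of entry (Study setting and population):** Cooperatives work with local collaborators "to engage smaller primary care practices in their regions". Trial status adds that "recruitment of practices is in progress".
- **Number (Study setting and population):** "The ESCALATES evaluation will include the approximately 1,500 primary care practices".
- **Question posed (Analytic strategy):** the rates sought are those "among a large sample (>1500) of small- and medium-size primary care practices".

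**The concern.** An estimate represents a national population only if practices across the country could have entered the sample in a way that allows generalisation, or if some stated adjustment links the sample to that population. The article describes neither. Instead it describes a programme cohort: regions chosen by grant award, practices recruited within them, and a target group defined partly by weak QI capacity. That last feature is plausibly related to performance on aspirin, blood pressure, cholesterol and smoking care, which is the quantity being estimated.

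What is at stake is how the answer to the first research question is read. The Impact section hopes the findings will inform a national extension system, and the Significance section claims unusually high external validity. A pooled rate labelled as national could be quoted as a benchmark for US small practices when it describes participants in one initiative.

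**Working it through.** The article gives no estimate, standard error or precision target for the baseline rates, so there is no figure of the plan to reproduce. The check is a comparison of the claim with the design text, one element at a time.

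1. **Geography.** The claim is national. The data come from seven regions covering 12 states: Midwest 3, New York City 1, North Carolina 1, Northwest 3, Oklahoma 1, Southwest 2, Virginia 1, and 3 + 1 + 1 + 3 + 1 + 2 + 1 = 12. Practices outside these regions cannot enter. The regions were set by funding and are not described as a sample of the country.

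2. **Population.** The claim names small- to medium-size primary care practices. The Background restricts the supported practices to those with limited QI capacity. The second group is part of the first.

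3. **Entry.** Practices are engaged and recruited by Cooperatives and their local partners. Those that join have agreed to take part in an improvement programme, so willingness also separates them from other small practices in the same regions.

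4. **Question.** The research question asks for rates in a large sample of practices and names no national target. It can be answered as posed. Only the later sentence adds the national claim.

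5. **Limitations.** Three are given: incomplete harmonisation of measures, loss to follow-up or inability to supply data, and dependence on extractable disparities data. The comparison planned under the second is between practices that drop out and those that remain. Nothing compares recruited practices with those not recruited. If harmonisation fails, the stated fallback is to analyse a subset of practices, which would narrow the base further.

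Elements 1 to 3 each conflict with the claim, and element 5 does not repair it. About 1,500 practices will improve precision, but numbers do not remove a bias that comes from which practices could and did enter.

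**The case against.** The strongest reply is that this is one descriptive clause. The research question is answerable without it, and no model in the article uses a national rate. That stands as a limit on scope. The room-for-improvement statement refers to the study period and so to the enrolled practices, for which their own baseline rates are the right quantity. A reader might infer that this assessment, or the regression and difference-in-differences analyses, is undermined. The document does not support that.

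A reader might also infer that the pooled interval would almost never contain the national rate. With an assumed between-practice SD of 15 points, SE = 15/√1500 = 0.39, and an assumed 3-point difference between participants and other small practices would be 3/0.387 = 7.7 SEs. The document gives neither number. The calculation also treats practices as independent, although the longitudinal analysis section names Cooperative and region as clustering levels. With seven equal Cooperatives of 1500/7 ≈ 214 practices, the design effect is 1 + 213.3 × ICC:

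| Assumed ICC | Design effect | SE (points) | 3 points in SEs |
|---|---|---|---|
| 0.02 | 5.3 | 0.89 | 3.4 |
| 0.05 | 11.7 | 1.32 | 2.3 |
| 0.10 | 22.3 | 1.83 | 1.6 |

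The result depends entirely on the assumptions. The sign is open too: limited QI capacity could lower the rates, and willingness to enrol could raise them.

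Finally, it is tempting to say that there is no sampling frame and that no weighting is planned. The article mentions neither, but it is a condensed account, and its silence does not show that the full protocol or analysis plan lacks them. The point does not need that inference. It rests on what the article states about regions, recruitment and QI capacity.

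On missing data the article does make provision: it will track practices that take part but cannot supply data, seek the reasons, and allow chart review as well as programmed extraction. This deals with losses among recruited practices, not with selection into the sample.

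**Conclusion.** The claim of national representativeness is wrong as written. The article asserts a property that its own account of regions, target practices and recruitment does not give the sample, and no other section corrects this. This is a positive statement in conflict with the design, not a detail left to another document.

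The size and direction of any bias cannot be determined from the document, and this conclusion assumes no value for either. The consequence is confined to the target of inference for the first research question: the pooled baseline rate describes participating practices and does not estimate a national rate. The analyses of participating practices stand.

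**What to change.** In Cross-sectional research questions (baseline), replace the phrase claiming nationally representative estimates with: estimates for participating EvidenceNOW practices in seven regions covering 12 states. Make no national inference from the pooled rate in reports of the baseline results.

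Add a sentence to the Limitations saying that practices were recruited by regional Cooperatives and were meant to have limited QI capacity, so that their rates may differ from those of other small practices in a direction that cannot be predicted.

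Reporting rates by Cooperative, with the numbers recruited and the numbers supplying baseline data, would help readers but is optional. No data collection, model or sample size changes. The cost is a less favourable claim.

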### Longitudinal research questions

#### Identifying and distinguishing Cooperatives’ intervention approaches

A central aspect of Cooperatives’ interventions involves developing the infrastructure needed to rapidly deliver external support to approximately 250 practices. The ESCALATES team will analyze qualitative data to characterize the specifics of each Cooperative’s external support strategy and to create typologies that distinguish interventions and characterize the infrastructure Cooperatives develop to support practices. Typologies are a system for categorizing Cooperatives and their participating practices into groups based on a set of salient characteristics. Groupings will be quantified and become variables in subsequent quantitative analyses. This mixed methods procedure is to converge the data using data transformation so that a quantitative analysis can be used based on quantifying the qualitative findings. To do this, the ESCALATES team will analyze qualitative data using a grounded theory approach [54–56] to characterize the factors that emerge as barriers/facilitators to implementation (e.g., practice, context/environmental, and intervention characteristics), how and by whom external support is delivered and the factors that affect this, and what changes practices implement and why. We will make comparisons across Cooperatives, paying particular attention to factors leading to a Cooperative excelling or struggling in response to the intervention. We will create matrices to display data for comparative analyses as suggested by Miles and Huberman [57]. As the ESCALATES team develops initial classifications, these will be shared with Cooperatives as a form of “member checking,” a qualitative research verification step accomplished by asking key informants to validate study findings [58–61]. This analytic strategy will result in rich interpretive summaries of each Cooperative’s intervention, particularly with respect to core features of intervention strategies and other characteristics the ESCALATES team identify as important to D&I. Summaries and matrices will lead to the development of a series of typologies that categorize and transform important aspects of the Cooperatives and their interventions into quantitative variables. For example, external support (e.g., practice facilitation, expert consultation), mode of intervention (e.g., face-to-face, email, phone), frequency (number) and duration (length) of contacts might be made into a composite variable to represent intensity of external support for use in subsequent quantitative analyses.

#### Effect of intervention strategies on change in outcomes

Examining the effectiveness of external support interventions will involve estimating differences in ABCS and practice capacity outcomes for different intervention strategies received by practices engaged in each Cooperative, as well as differences in practice implementation. Intervention strategies will be compared to each other and/or to a control group of practices using a differences-in-differences (DID) approach [62]. The DID model is a flexible approach which can accommodate different study designs Cooperatives may propose to evaluate their own interventions. Conceptually, cluster-randomized designs, interrupted time studies, and step-wedge designs can be nested within the DID framework. The primary requirements are the inclusion of baseline (pre-intervention) data and data from a control group. In addition to examining the effectiveness of intervention typologies as assigned, we will also conduct sub-analyses that include differing levels of fidelity to quality improving strategies practices use. The DID approach has been frequently used by health services researchers and economists to account for potential secular effects and changing policies that would affect both intervention and control groups over time, while adjusting for potential confounders [7, 63–68].

The overall analysis to assess intervention strategies on ABCS performance can be considered as shown in the equation$$ {\boldsymbol{Y}}_{\boldsymbol{it}}=\boldsymbol{f}\left(\boldsymbol{\alpha} +{\displaystyle \sum_{\boldsymbol{j}=1}^{\boldsymbol{r}}}{\boldsymbol{\beta}}_{\boldsymbol{j}}{\boldsymbol{I}}_{\boldsymbol{j}}+\boldsymbol{\delta} {\boldsymbol{\tau}}_{\boldsymbol{j}}+{\displaystyle \sum_{\boldsymbol{j}=1}^{\boldsymbol{r}}}{\boldsymbol{\theta}}_{\boldsymbol{j}}{\boldsymbol{I}}_{\boldsymbol{j}}{\boldsymbol{\tau}}_{\boldsymbol{j}}\right), $$

where: ***Y***
_***it***_ represents clinic *i’*s performance on an outcome measure (i.e., one of the ABCS measures, mean adaptive reserve score) at time *t*,; ***I***
_***j***_ represents a dummy variable (intervention strategy received variable described above) taking a value of 1 if the clinic was involved in intervention *j* and zero otherwise; and ***τ***
_***j***_ is a dummy variable taking a value of 1 if the observation took place after the intervention and 0 otherwise, and *f* represents a general function that captures our intent to model performance through a beta regression for ABCS measures and linear regression for practice capacity outcomes. The coefficient ***α*** is an overall intercept representing average baseline performance for all clinics; ***β***
_***j***_ represents the incremental baseline performance differential between clinics in typology *j*, and ***δ*** represents the change in performance pre- and post-intervention, for all clinics. The ***θ***
_***j***_ coefficients are the coefficients of interest, as they capture the relative performance improvement for each group using intervention typology *r*. The qualitative analyses described above will produce *r* variables (e.g., high, medium, low intensity support strategy) (*r* lying somewhere between 3 and 6). In this model, control groups serve as the reference. This equation can be adapted to include additional dummy variables for each time period or a continuous variable to capture linear time trends as well as fixed effects (equivalent to dummy variables) for practices.

The ESCALATES team will use two-way fixed effects models (i.e., a fixed effect for each practice and for each time period) so the results do not rest on some of the stricter assumptions required for random effects models. However, we will also conduct analyses by introducing a practice random intercept and slope to allow intervention effects to vary across practices in the different study arms. This approach explicitly models different clustering levels (e.g. Cooperative, region, practice) [63]. In this case, rather than treating the practice as a nuisance factor, this approach allows each practice to respond differently over time to the intervention and allows the ESCALATES team to estimate those changes and study the heterogeneity of effects due to variation in context across Cooperatives and differences across practices within each Cooperative.

The analyses described above will be conducted for each ABCS measure. In addition, ESCALATES will produce a model that pools all measures and uses measure-specific fixed effects, which will allow for an assessment of an “overall” effect of the interventions.

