## Methods/design

### Study design

ESCALATES is a prospective mixed methods observational comparative study using a range of qualitative and quantitative data collection approaches to accomplish the study aims (see Table 1). The ESCALATES study is informed by the Learning Evaluation approach in that we will analyze clinical relevant outcome measures that do double-duty as performance measures for practices, thereby fostering learning for practices; we collect and analyze real-time quantitative and qualitative data on important contextual factors, and the goal is to foster cross-Cooperative learning from process and outcome data [40]. Table 2 list key elements of the evaluation.

**Table 1 Tab1:** Data Sources

	Description	Level	Source of data	Type of data	Frequency
Cooperative grant proposals	Cooperative’s initial plan for implementation	Cooperative-level	Collected by ESCALATES team with Cooperatives assistance	Qualitative	Pre-grant award
Other documents	Documents Cooperative’s develop (ex: recruitment materials, PF curricula, etc.)	Cooperative-level	Collected by ESCALATES team with Cooperatives assistance	Qualitative	Throughout study period
Online diaries	Online journal; approximately 5-13 people per Cooperative; document implementation experiences	Cooperative-level	Online, interactive communication platform	Qualitative	Post 2x mo.; Start-up to post-implementation
Cooperative site visits	To observe and understand how interventions are implemented	Cooperative-level	Fieldnotes	Qualitative	Annually years 2 and 3
Sustainability site visits	To understand how/which parts of the D&I infrastructure is sustained beyond the life of the grant	Cooperative-level	Fieldnotes	Qualitative	Year 4
Semi-structured interviews	To understand barriers/facilitators of specific aspects of implementation; experience with intervention; mechanisms of change	Cooperative-level	Interviews with Cooperative key stakeholders	Qualitative	Annually with 5-8 people or as needed
Clinical quality measures (ABCS)	Proportion of patients meeting ABCS and data source (e.g. EHR, chart review)	Aggregated by Practice	Medical Record (EHR extraction/chart reviews); collected by Cooperatives; shared with ESCALATES	Quantitative	Baseline through end of study; Quarterly

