#### Assessing contextual factors and heterogeneity of intervention effects

To assess heterogeneity of intervention effects, ESCALATES will identify factors associated with substantial improvement for some practices and lack of change or worsening performance for others. For instance, the ESCALATES team may observe that practices receiving the external support strategy of data feedback/benchmarking resulted in significantly improved ABCS performance measures over time as compared to a group of practices receiving expert consultation or a control group of practices. On further analysis of the effect of type of practice (moderator) on the observed association, however, the ESCALATES team may find that practices affiliated with large health systems showed greater improvements in ABCS measures than independent practices. Thus, this effect modification analysis is designed to capitalize on the large sample size and diversity of practices and several different intervention strategies that will be tested by Cooperatives to identify heterogeneity of ABCS measures and practice capacity measures of association across levels of modifying variables. Another key variable of this analysis involves the fidelity with which practices implement QI tools to address ABCS. Data on implementation fidelity will be collected using the external support/practice implementation tracking data. ESCALATES will create meaningful categories of this variable to include in the modification analysis, such as practices that implement QI tools consistently and to a high degree of fidelity will likely perform better at improving ABCS and practice capacity than those that do not, even when both groups of practices receive the same external support.

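### The main difference-in-differences model removes confounding of level but not of change, so theta_j needs period-by-baseline-characteristic terms where strategy groups are not randomized

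*Protocol article*

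**What the plan says.** All of this is in the protocol article. Study design states that "ESCALATES is a prospective mixed methods observational comparative study". Under Effect of intervention strategies on change in outcomes, "Intervention strategies will be compared to each other and/or to a control group of practices", and the article notes that "cluster-randomized designs, interrupted time studies, and step-wedge designs can be nested within the DID framework". The portfolio may therefore mix randomized and non-randomized contrasts.

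The displayed equation has an intercept, strategy indicators, a post-intervention indicator and their products. Of the product terms theta_j it says that these "coefficients are the coefficients of interest, as they capture the relative performance improvement for each group". The extensions it names are these: "This equation can be adapted to include additional dummy variables for each time period or a continuous variable to capture linear time trends", together with practice fixed effects. It then commits to a main model: "The ESCALATES team will use two-way fixed effects models (i.e., a fixed effect for each practice and for each time period". A model with a practice random intercept and slope is additional.

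On confounding, the same section says that DID has often been used by researchers in the field "to account for potential secular effects and changing policies that would affect both intervention and control groups over time, while adjusting for potential confounders".

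Practice characteristics are tied to time only in the section on contextual factors and heterogeneity. There they enter as moderators in three-way interactions, singly or as a weighted composite.

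**The concern.** Theta_j measures relative change, so what threatens it is a characteristic linked both to the strategy a practice gets and to how fast that practice would have changed anyway. A practice fixed effect does not touch this. Neither does a period effect, which removes only what is common to all practices. The equation and its named extensions contain no term that lets practices with different baseline characteristics follow different time courses.

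Strategies are compared with each other across an observational portfolio, so groups may well differ in ownership, size or EHR capacity. If such a characteristic also predicts change, a strategy given mainly to fast-changing practices will look effective without being so. One given mainly to slow-changing practices will look useless. The article's central product, a judgement on which strategies work best, rests on these coefficients.

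**Working it through.** The article states no sample-size calculation, significance level or standard deviation, so there is no figure of its own to reproduce. The only input taken from it is the size, about 1,500 practices (Study setting and population). All other inputs below are assumptions, including a two-sided 5% level and practices treated as independent.

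**1. The bias.** Let X be a binary baseline characteristic with extra pre-to-post change g, and let its prevalence differ by d between a strategy group and the reference. In a balanced panel, the two-way fixed-effects estimate equals the difference between groups in mean change, so

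E(estimate) = theta_j + d × g.

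It is unbiased if d = 0 or g = 0. The level of X does not enter, because the practice effect removes it.

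**2. What enters the model and what drops out.** This was checked on a design matrix with 60 practices, 5 periods, explicit dummies and a true effect of 0.

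| Model | Columns | Rank | Estimate |
|---|---|---|---|
| Two-way fixed effects | 65 | 65 | 0.0240 |
| plus X as main effect | 66 | 65 | 0.0240 |
| plus X × post | 66 | 66 | 0.0013 |

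The main effect of X is collinear with the practice effects and changes nothing. The product with time does the work.

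**3. Illustration.** Assume g = 3 points, 60% versus 20% with the characteristic, five groups of 300 practices, and an SD of change of 11.3 points.

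- Bias = 3 × (0.60 − 0.20) = 1.2 points.
- SE = 11.3 × √(2/300) = 0.92.
- 1.2 / 0.92 = 1.30, and P(Z > 1.96 − 1.30) is about 25%.

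A simulation of this case (2,000 runs, true effect 0) gave a mean estimate of 1.19, SE 0.93 and 25% rejection. With the characteristic-by-period term it gave −0.01, SE 0.96 and 4.7%. The SE ratio is 0.96 / 0.93 = 1.03.

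**4. Range.**

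- Low end: bias 0.6, 200 per group, SD 15. SE = 15 × √(2/200) = 1.50, ratio 0.40, rejection 7%.
- High end: bias 2.0, 300 per group, SD 10. SE = 10 × √(2/300) = 0.82, ratio 2.45, rejection 69%.

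**5. A second set of assumptions.** Here there were two groups of 750, one baseline and eight later quarters, a residual SD of 0.05 on the proportion scale, and 200 runs per cell. The SD of change is then 0.05 × √(1 + 1/8) = 0.053, much smaller than above, so the same bias is detected more often.

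| d | g | d × g | Mean estimate | Rejection |
|---|---|---|---|---|
| 0.2 | 0.02 | 0.004 | 0.0040 | 32% |
| 0.4 | 0.02 | 0.008 | 0.0080 | 81% |
| 0.2 | 0.05 | 0.010 | 0.0102 | 93% |
| 0.4 | 0.05 | 0.020 | 0.0203 | 100% |

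With X × time added, the mean estimate was within 0.0005 of zero in every cell and rejection lay between 2.5% and 8.5%. With d = 0 or g = 0 there was no bias.

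**6. Scale.** The ABCS models are beta regressions, where the same argument applies on the linear-predictor scale. One small beta-regression data set (60 practices, expected bias 0.130 on the logit scale) moved from 0.0215 (SE 0.0673) to −0.0838 (SE 0.0736) when the term was added. The shift of 0.105 has the expected direction and rough size, but one data set with such standard errors proves nothing by itself.

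**The case against.** Several points on the other side stand.

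- **The sentence on confounders.** A reader might infer that the article promises covariate adjustment its model cannot deliver. The sentence reports how DID is used in the literature. It supports the choice of method but does not say that the displayed equation adjusts for listed covariates.
- **Fixed effects do adjust.** A reader might infer that adjustment here is empty. It is not: all stable confounding of level is removed. The remaining gap is the usual parallel-trends assumption, and the practice effects do not create it.
- **The affiliation example.** The article imagines that "practices affiliated with large health systems showed greater improvements in ABCS measures than independent practices". A reader might take this as an admission of a background trend. It is put forward as effect modification, a strategy working better in some practices, and does not show that affiliated practices improve regardless of strategy.
- **Repeated survey.** The practice survey is given three times, so a characteristic that changes is not strictly collinear with the practice effects. But values measured after the intervention may be consequences of it, so they are no safe substitute for baseline values.
- **Other models.** A hierarchical three-way model contains a characteristic-by-time term, and a composite moderator is planned as well. These models test for whom a strategy works and do not define the main theta_j. Practice-characteristic moderators are also to be drawn from those associated with baseline level, not with trend. A random slope does not help if slopes are related to strategy.
- **A condensed article.** Covariate lists are often left to a fuller plan, which is not shown. Here, though, the equation, its extensions and the main model are all stated.
- **The simulations.** They place all confounding in one known variable, so recovery after adjustment is built in. They show the mechanism and not the likely size in this study.

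**Conclusion.** The point holds in a limited form. As specified, the main model adjusts for time-constant confounders in level only. Any trend difference tied to a characteristic that is unbalanced between non-randomized strategy groups passes in full into theta_j. Contrasts between arms randomized within a Cooperative are protected.

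The bias needs both imbalance and a differential trend, and the article shows neither to be present. The 1.2 points, the 25% and the 7% to 69% range are illustrations under assumed trend differences, imbalance and SD. They are not estimates for this study. What is certain is the structure, bias = d × g, and that neither the moderator analyses nor the random-slope model removes it from the main estimate. Since data for a better-specified model are already to be collected, the change is worth making before the longitudinal analysis.

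**What to change.** In the main two-way fixed-effects model, add period-by-baseline-characteristic terms for a short prespecified list: ownership, practice size and EHR capacity, all named under Practice surveys. Add rural or underserved status only if its source is confirmed, because the article mentions it under Practice site visits as a sampling characteristic and does not list it as a survey item. Use baseline values only. Report theta_j with and without the terms, so that readers can see how far the estimate depends on them.

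Keep the sentence on confounders but qualify it: in this model, time-constant confounders are adjusted for in level, and in change only through the added terms.

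The cost is a few more parameters and a slightly larger SE: about 3% with one covariate in the illustration, possibly more with several. The three survey items need no new data. Unmeasured causes of differential trend would remain.
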